### **Secondary objectives**

4. To assess the seroprevalence according to vaccination status among NH residents and staff in Belgium at month 0 and at every follow-up visit in the cohort at month 2, 4, 6, 8 and 10.

The seroprevalence among NH residents and staff in Belgium at month 0, and follow-up in the cohort at month 2 (and if relevant at month 4, 6, 8, and 10), will be reported according to the vaccination status (Number of shots: 0, 1 or 2) and for the subgroups ‘with’ and ‘without’ a history of self-reported SARS-CoV-2 infection, averaged over NHs based on a GEE analysis with exchangeable covariance structure.

5. To assess the risk of getting a SARS-CoV-2 infection since vaccination between:
  - Residents and staff
  - Seropositive and seronegative participants at all timepoints
  - Individuals with or without previous self-reported SARS-CoV-2 infections
  - Adjusted for the updated vaccination degree of NH at all timepoints

For vaccinated participants only, a survival analysis will be performed to investigate the time (in days) to a SARS-CoV-2 infection since vaccination between sero-positive and -negative

participants at all time points. A participant is considered to have an event when the participant had a positive PCR test result (or a positive antigen rapid test, or a positive CT scan, or a positive saliva test in absence of a PCR test). The survival or censoring time (in days) is registered since 14 days after being fully vaccinated (full dose regimen) until first event (or censoring moment). If the proportional hazard assumption holds, a stratified (by NH) Cox proportional hazards regression model will be used to model the hazard of SARS-CoV-2 infection between sero-positive and -negative participants at all time points (modelled by the inclusion of a time-varying seropositivity status), adjusted for type of participant, history of self-reported SARS-COV-2 infections, and a time-varying NH vaccination degree. The analysis will be performed stratified by type of participant or other variables, if the proportional hazard assumption does not hold.

6. To assess the proportion of confirmed COVID-19 deaths and non-COVID-19 related deaths since vaccination and the time until death (within the study timeframe) between sero-positive and -negative participants for NH residents

For vaccinated NH residents only, a survival analysis will be performed to investigate the proportion of deaths within the study follow-up and the time (in days) to a confirmed COVID-19 death since 14 days after being fully vaccinated (full dose regimen). The survival or censoring time (in days) is registered since 14 days after being fully vaccinated until first event (or censoring moment). A non-COVID-19 related death will be considered as a competing risk in the analysis. If the proportional hazard assumption holds, a stratified (by NH) Cox proportional hazards regression model will be used to model the cause-specific hazards between seropositive and seronegative residents. The latter will be included as a time-varying covariate. A history of self-reported SARS-COV-2 infections, a time-varying NH vaccination degree, province, age, gender, care profile, and presence of COVID-specific comorbidities will be

considered for model adjustment.

7. To assess the duration of SARS-CoV-2 specific antibody response (seroreversion/no antibody response) since 14 days after being fully vaccinated among NH residents and staff in Belgium.

The duration of SARS-CoV-2 specific antibody responses among NH residents and staff in Belgium will be modelled by means of an interval-censored survival analysis. Seroreversion will be defined as a negative rapid test result after at least one positive rapid test result or as two succeeding negative test results (implying the participant did not seroconvert after vaccination within two to four months). The time interval to seroreversion/no response is the time interval between 14 days after the (second) vaccination date (full dose regimen) and the first test moment of a negative test result after at least one positive rapid test or of the two succeeding negative rapid test results. As a sensitivity analysis, the event will also be defined as two succeeding negative rapid test results (whether or not after at least one positive rapid test result), if the rapid test result would turn out to be unstable.

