# **1. Background and objectives**

Statistics on reverse-transcriptase polymerase chain reaction (RT-PCR)-confirmed SARS-CoV-2 cases and deaths aid in monitoring the dynamics of disease propagation. However, diagnostic RT-PCR testing is far from ideal when trying to estimate the proportion of the population infected, a key indicator for public health decision making in the ongoing COVID-19 pandemic (Roda et al., 2020). For example, mildly affected or asymptomatic individuals are often not screened. Furthermore, RT-PCR-based testing yields only an epidemiological snapshot, because it fails to detect persons that already cleared SARS-CoV-2, making it difficult to infer the true proportion of the population that has been infected. Also, during the first months of the pandemic, most countries, including Belgium, did not have an adequate RT-PCR testing capacity for screening of anyone suspected or at risk of infection with SARS-CoV-2. As a result, the number of confirmed SARS-CoV-2 infections is largely underestimated (Verity et al., 2020).

In this context, seroprevalence surveys are of utmost importance. These studies can assess the proportion of the population that has already developed SARS-CoV-2 antigen-specific antibodies () and might potentially be protected against subsequent infection (Lipsitch et al., 2020). As recommended by WHO, monitoring changes of seroprevalence over time is also crucial to anticipate the dynamics of the pandemic and plan an adequate public health response (WHO, 2020). So far, seroprevalence data are available in Belgium for the general population (4.3%; blood donors) (Rode Kruis, 2020), ITG (8.4) (MAY 2020) and hospital staff (6.4%) (Steensels et al., 2020). Additionally, a national study among health care workers in Belgian hospitals showed an anti-SARS-CoV-2 IgG seroprevalence of 7.7% (Mortgat et al., 2020). Few data are available concerning the SARS-CoV-2 seroprevalence among nursing home (NH) residents and staff in Belgium, although these populations suffered from severe local SARS-CoV-2 outbreaks. Elderly are at high risk to develop severe cases of COVID-19, as 27% of the

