total of the 9878 COVID-19 fatal cases in Belgium (between March 8th and June 2nd 2020) were reported from nursing homes (Sciensano, 2020). In May 2020, a pilot baseline seroprevalence study was conducted in NHs among Flanders, which showed that 24,5% and 19,1% of respectively NH residents and staff developed SARS-CoV-2 antigen-specific antibodies. Among the nine different nursing homes included in this study, a large variation in seroprevalence was seen ranging from 0,0% to 38,4% and 5,2% to 31,0% for residents and staff respectively (*unpublished data*). However, the degree of seroprevalence and sero-incidence for NHs in Brussels and Wallonia remains unknown. Furthermore, the pilot study conducted in May 2020 assessed the seroprevalence 4 to 6 weeks after the peak incidence of the first epidemic wave. Additionally, when a COVID-19 vaccination will be implemented, it will be of crucial importance to monitor the seroprevalence in Belgian nursing homes and assess the degree of persistence of this vaccine-induced immune response.

Therefore, our major study goals are to assess the current seroprevalence of SARS-CoV-2 in NH residents and staff in Belgium with subsequent 2-monthly follow-up of the sero-incidence over a period of 10 months. Furthermore, many questions remain unsolved about the proportion of asymptomatic cases of SARS-CoV-2 antibody positive NH residents and staff (and about their individual risk factors). Our secondary study goal is to gain additional insights on the association between seropositivity, clinical manifestation and COVID-19 disease outcome.

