If the proportional hazard assumption holds, a stratified (by NH) Cox proportional hazards regression model will be used to model the cause-specific hazards between vaccinated and

non-vaccinated residents, adjusting for history of self-reported SARS-COV-2 infections, and a time-varying NH vaccination degree. Propensity score methods will be applied to reduce the effects of confounding.

10. To assess the duration of SARS-CoV-2 specific antibody responses (seroreversion/no antibody response) since self-reported infection in a non-vaccinated residents/staff.

If sufficient non-vaccinated participants with self-reported infection would be available in the random selected sample, a survival analysis for interval censored data will be performed to investigate the time (in days) to a SARS-CoV-2 specific seroreversion/no antibody response since self-reported, natural SARS-CoV-2 infection. A participant is considered to have an event (seroreversion/no antibody response) during the interval between a positive and a negative rapid test result during the follow-up visits, or between the between the positive test date and the first visit date in case of a negative rapid test at the first test date. If the rapid test results would turn out to be unstable, a sensitivity analysis will be performed and an event is considered after two succeeding negative rapid test results during the follow-up study visits. The survival or censoring time will be expressed as an interval in days between the positive test date until the visit date with first event (or censoring moment). A Cox proportional hazards regression model for interval censored data will be used to model the hazard of a SARS-CoV-2 specific seroreversion/no antibody response since natural infection adjusted or stratified for staff and residents.

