## Individuele vragenlijst (in te vullen bij aanvang studie)

### **Versie voor deelnemende medewerkers:**

1. Gelieve uw uniek studienummer in te vullen. (cfr lijst met random cijfers en studienummers, terug gestuurd door het onderzoekscentrum UGent)
2. Gelieve uw leeftijd in te vullen.
3. Wat is uw geslacht? M/V
4. Wat is uw functie (hoofdactiviteit) binnen het WZC
  - Zorg
  - Administratie
  - Paramedisch (kinesitherapeut, ergotherapeut, ...)
  - Poetswerk
  - Keuken
  - Kapper/pedicure
  - Andere (vrijwilliger, animatie, ...): (*Invulmogelijkheid*)
5. Werkt u op een afdeling voor bewoners met dementie? Ja / neen
6. Lijdt u aan 1 van volgende aandoeningen? Duid aan wat van toepassing is (meerdere antwoordmogelijkheden).
  - Hart- en vaatziekten
  - Diabetes
  - Hoge bloeddruk (hypertensie)
  - Ernstige long-/hart-/nierziekte
  - Verzwakt immuunsysteem (immunosuppressieve aandoeningen) of immuunsysteem verzwakt door langdurig gebruik van immunosuppressieve medicatie (vb. chemotherapie, transplantatiepatiënten, immunosuppressieve reumamedicatie, corticoïden...)
  - Actieve kankeraandoening
  - Geen van bovenstaande
- Bent u gevaccineerd tegen COVID-19?
  - Ja, 1 dosis
  - Ja, 2 dosissen
  - Neen
  - Zo ja, welk vaccin kreeg u toegediend
    - Het AstraZeneca/Oxford vaccin
    - Het BioNtech-Pfizer vaccin
    - Het Moderna vaccin
    - andere
  - Zo ja, datum van vaccinatie (eerste spuit).

7. Bent u dit seizoen gevaccineerd tegen griep? (*Deze vraag zal terugkomen in de vragenlijst bij laatste follow-up*)
8. Bent u ooit getest geweest op het coronavirus (via PCR/ag-sneltest/of radiologisch via CT-scan)? Ja/Nee
9. Zo ja, Bent u ooit **positief** getest geweest op het coronavirus? (Meerdere antwoordmogelijkheden)
  - Ja, via PCR-test (test waarbij men via een neuswisser een staal afneemt en u na labo-analyse het resultaat krijgt)
  - Ja, via antigeen sneltest (test waarbij men via neuswisser een staal afneemt en men binnen het kwartier het resultaat kan aflezen)
  - Ja, radiologisch, via een CT-scan
  - neen
9. Zo ja, datum van 1ste positieve PCR-test of sneltest (bij benadering)?
10. Indien COVID-19 radiologisch bevestigd werd via een CT-scan, vermeld de datum van deze CT-scan.
11. Indien u ooit positief getest bent, waar lag de vermoedelijke bron van besmetting?
  - Binnen het WZC
  - Buiten het WZC
  - De bron van de besmetting was mij onbekend

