#### **6.4.4. Data collection and analysis**

Only biological specimens will be collected. No additional questionnaire will be needed. The collected dry blood spots will be send back to Ghent University and saved in a study-specific biobank. The collected samples will be analyzed using an Enzyme-Linked Immuno Sorbent Assay (ELISA) for (semi)-quantitative detection of anti-SARS-CoV-2 specific antibodies (anti-S1/anti-NCP). The Dry Blood Spot samples will be pseudonymized.

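### Previous infection is classified by self-report alone, so the group without a reported history contains undiagnosed infections; the anti-NCP results already planned should be added as a second, prespecified definition

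*Protocol*

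**What the plan says.** In section 3.2 of the protocol, objective 4 tabulates seroprevalence by 0, 1 or 2 doses and by "a history of self-reported SARS-CoV-2 infection, averaged over NHs". Objective 5 lists as a contrast "Individuals with or without previous self-reported SARS-CoV-2 infections", and its Cox model is "adjusted for type of participant, history of self-reported SARS-COV-2 infections, and a time-varying NH vaccination degree". Objectives 8 and 9 adjust for the same history, and objective 6 considers it for adjustment.

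Section 3.2 gives no fuller definition, but a test-based one is the natural reading. The baseline staff questionnaire (Appendix 6.3) asks "Bent u ooit getest geweest op het coronavirus (via PCR/ag-sneltest/of radiologisch via CT-scan", then whether any such test was positive, and asks about symptoms separately. For objective 10, where infection is also self-reported, the protocol writes: "The survival or censoring time will be expressed as an interval in days between the positive test date until the visit date". Section 2.7.2 allows residents' data to come from the head nurse or a representative.

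Section 1 says that in the first months most countries, Belgium among them, "did not have an adequate RT-PCR testing capacity for screening of anyone suspected or at risk of infection with SARS-CoV-2". It adds that mild and asymptomatic cases are often missed and that confirmed counts fall far short of true infections.

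Appendix 6.4 takes a dried blood spot from each participant alongside every rapid test and plans an ELISA "for (semi)-quantitative detection of anti-SARS-CoV-2 specific antibodies (anti-S1/anti-NCP". The stated purpose is a sub-study that follows both vaccine-induced and infection-induced antibodies. No analysis in section 3.2 uses an ELISA result.

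**The concern.** The protocol's own background gives the reason why a history built on reported tests will miss infections. People who were infected but never tested positive fall into the group without a history, so the self-report split does not separate infected from uninfected people.

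In objective 4, the 0-dose and 1-dose cells without a history then contain some antibody that comes from infection. In objective 5, the comparison of people with and without previous infection has a mixed reference group. In objectives 6, 8 and 9, adjustment for previous infection is incomplete.

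The rapid test does not repair this. Section 2.7.1 counts any IgM or IgG as positive, with no rule that separates vaccination from infection. The limitations in section 4.3 do not mention the problem.

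**Working it through.** The plan gives no figure for the share of infections that self-report captures, so there is none to reproduce. The sample size (69 × 44 = 3036) is not in question.

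Inputs from the protocol:
- True prior infection, π: the May 2020 pilot in section 1, where "24,5% and 19,1% of respectively NH residents and staff developed SARS-CoV-2 antigen-specific antibodies". As an alternative, the planning value of 0.5 in section 2.5, read as if it were all infection.
- Rapid-test sensitivity 0.929 and specificity 0.963 (section 4.3), so the false-positive floor is 1 − 0.963 = 0.037.

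Assumptions, not in the documents:
- The share of infections diagnosed and reported, d, is 0.3 to 0.7, with no false reports.
- Infected people stay detectable, and π is the same in each dose group.
- Among uninfected people, 50% test positive after one dose and 90% after two.

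Share of the group without a history that was in fact infected: c = π(1 − d)/(1 − πd). For residents at d = 0.3, c = 0.245 × 0.7/(1 − 0.245 × 0.3) = 0.1715/0.9265 = 0.185.

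| π | d = 0.3 | d = 0.5 | d = 0.7 |
|---|---|---|---|
| 0.245 (residents) | 0.185 | 0.140 | 0.089 |
| 0.191 (staff) | 0.142 | 0.106 | 0.066 |
| 0.5 (planning value) | 0.412 | 0.333 | 0.231 |

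Widening d to 0.25–0.90 gives 2% to 20% at the pilot values and 9% to 43% at π = 0.5.

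Effect on the objective 4 cells without a history, for residents:
- 0 doses: 0.929c + 0.037(1 − c)
- 1 dose: 0.929c + 0.5(1 − c)
- 2 doses: 0.929c + 0.9(1 − c)

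| | c = 0 | d = 0.7 | d = 0.5 | d = 0.3 |
|---|---|---|---|---|
| 0 doses | 0.037 | 0.116 | 0.162 | 0.202 |
| 1 dose | 0.500 | 0.538 | 0.560 | 0.579 |
| 1 dose minus 0 doses | 0.463 | 0.422 | 0.398 | 0.377 |
| 2 doses | 0.900 | 0.903 | 0.904 | 0.905 |

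The difference equals 0.463(1 − c), so it always shrinks. For staff it runs from 0.432 (d = 0.7) to 0.397 (d = 0.3).

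Effect on objective 5, approximated as a ratio of average hazards: observed HR = HR/[(1 − c) + HR × c]. With a true HR of 0.20 (assumed) and residents at d = 0.3, this is 0.20/(0.815 + 0.037) = 0.235. Over d = 0.3 to 0.7 the observed HR is 0.21 to 0.23 at the pilot values and 0.25 to 0.30 at π = 0.5.

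**The case against.** The best defence is that the protocol does what it says. It labels the variable as self-reported throughout and never calls the remaining group infection-naive. Refinement of a covariate could also sit in a statistical analysis plan that is not shown. The labelling defence stands, and there is no internal contradiction. But section 3.2 fixes the variable as self-report, and the planned alternative is in the same document.

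Several stronger readings are tempting and should not be drawn:
- That testing was unavailable. Section 1 says only that capacity was inadequate in the first months. The baseline question covers any earlier test, and Table 1 places baseline in February 2021.
- That the vaccine is credited with infection antibody. The 1-dose level does rise, but the 0-dose level rises more, so the contrast between them falls. Objective 4 is descriptive, and section 3.2 says the study was not designed for vaccine effectiveness.
- That the blood-spot results are wasted. They have a sub-study purpose; they are unused only in section 3.2.
- That anti-NCP should replace self-report. In objective 4, removing people who are antibody-positive on blood from the same visit pushes the 0-dose cell towards the 0.037 floor by construction. It would also hide undetected infection, which section 1 treats as an open question.

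A timing objection also stands. Follow-up in objectives 5, 6, 8 and 9 starts 14 days after full vaccination. The Table of changes dates the start of vaccination to 5 January 2021, and first sampling is marked for February 2021. A month-0 or later spot may therefore follow the origin, and one infection could count as both history and event.

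Finally, the documents do not state outright that anti-NCP distinguishes infection from vaccination, and they give no accuracy for the ELISA on dried spots. These objections rule out anti-NCP as the sole main definition, but not as an added one.

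**Conclusion.** The concern holds in a limited form. Self-report alone leaves an unknown share of undiagnosed infections in the group without a history. That share is about 7% to 14% for staff and 9% to 18.5% for residents at the pilot seroprevalences, if 30% to 70% of infections were diagnosed. The direction follows from the protocol's background; the size rests on the assumed diagnosed share and cannot be fixed from the documents.

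The consequences are raised 0-dose and 1-dose cells, a smaller contrast between them, almost no change in the 2-dose cell, and modest attenuation in objective 5. The 0-dose cell is not empty: the Table of changes reports 15% of sampled staff unvaccinated in the first round. For residents it may be small, since section 3.2 allows for too few unvaccinated residents to analyse.

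Only secondary and tertiary objectives are affected. An added definition would let the study separate known, undetected and no detected previous infection using samples it already collects. It is worth making as a cheap improvement.

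**What to change.** Keep the self-report split. Add to section 3.2 a prespecified analysis that defines previous infection as a self-reported positive test or anti-NCP positivity on a dried blood spot:

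- Objective 4: use the month-0 spot and subdivide the group without a self-reported history by anti-NCP result, so that undetected infection stays visible. State that the 0-dose cell is then partly determined by construction.
- Objectives 5, 6, 8 and 9: use only spots taken on or before the time origin (14 days after full vaccination, or the corresponding nursing-home date for non-vaccinated participants), or code the status as time-varying from the spot date. Do not substitute the first available later spot as a baseline value.
- State the assumption that anti-NCP marks infection rather than vaccination, and that a negative result does not exclude an old infection.
- Add misclassification of self-reported history to section 4.3.

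The cost is wording and a merge of the sub-study ELISA file with the main file. No new samples or assays are needed beyond those planned in Appendix 6.4. The sponsor should confirm that the consent wording and participant codes permit the link. The protocol gives no ELISA timetable and section 4.1 names no ELISA cost, so the added analysis waits for those results. The rapid-test tables need not be delayed. Some misclassification will remain.
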